### Interventions

2.8

All enrolled participants will undergo hepatic arteriography 4–8 weeks following curative hepatectomy. With the patient in the supine position, standard aseptic preparation and sterile draping of the right groin will be performed. After local anesthesia with 5 mL of 2% lidocaine at the right femoral artery puncture site, a 5F arterial sheath will be inserted using the Seldinger technique. A 5F hepatic catheter will then be advanced into the celiac trunk for angiographic assessment. The hepatic arterial system, including the left and right hepatic artery branches, will be systematically evaluated to identify intrahepatic tumor staining. Detection of one or more foci of tumor staining will indicate that the initial hepatectomy did not meet criteria for curative resection, and such patients will be excluded. Participants without evidence of tumor staining will be randomly assigned to either the adjuvant TACE group or the intensive follow-up group.

In the adjuvant TACE group, superselective catheterization will be performed targeting the hepatic resection margin, followed by embolization using an emulsion of 50 mg lobaplatin and 3–5 mL ethiodized poppyseed oil. This regimen is based on prior RCTs demonstrating a reduction in postoperative HCC recurrence with adjuvant TACE.^30^^,^^31^ Polyvinyl alcohol embolic microspheres will not be utilized, as they are not part of the standard adjuvant protocol. In the intensive follow-up group, hepatic arteriography will be performed without administration of embolic or chemotherapeutic agents. Upon completion of the procedure, the catheter and arterial sheath will be removed, and manual compression will be applied to achieve hemostasis. Adjuvant TACE will be administered as a single session only.

### Assignment of interventions: allocation

2.9

#### Sequence generation

2.9.1

Randomization will be performed using computer-generated random number tables managed by Good Clinical Practice-compliant research centers at participating sites. Personnel responsible for sequence generation will have no involvement in study conduct. The interval between randomization and administration of adjuvant TACE will not exceed 1 week. During angiography, if tumor staining is identified in the remnant liver, TACE will be performed for clinical management; however, such participants will be excluded from the study.

#### Concealment mechanism

2.9.2

Allocation materials will be securely stored in sealed envelopes. Both the envelopes and the original documentation will be retained by the departmental records management unit for auditing and verification purposes.

#### Implementation

2.9.3

Following confirmation of eligibility, a designated study staff member will open the sealed envelope to obtain the assigned randomization number, which will determine allocation in a 1:1 ratio to either study group.

#### Blinding

2.9.4

This study adopts a multiple blinding design. The doctor performing interventional operations will be aware of treatment allocation, whereas investigators, participants and data analysts will remain blinded throughout the study until unblinding.

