### Strategies to improve adherence to interventions

2.7

The interventions employed align with established clinical practice. Participants in the adjuvant TACE group will receive treatment in accordance with CNLC recommendations,^29^ facilitating early detection of residual disease. Participants in the intensive follow-up group will avoid unnecessary treatment-related costs and potential adverse effects. The study will be conducted in accordance with GCP and applicable ethical standards. Investigators will maintain consistent and thorough communication with participants to promote adherence, reduce loss to follow-up, and minimize missing data. Prior to enrollment, investigators will provide a detailed explanation of study procedures, potential benefits, associated risks, and participant rights, including the right to withdraw consent at any time without consequence. Enrollment will proceed only after written informed consent has been obtained.

All analyses will follow the intention-to-treat principle. Participants who discontinue treatment or withdraw from the study prior to completion of the protocol-specified regimen will be encouraged to continue follow-up and complete all scheduled assessments. At the time of discontinuation or withdrawal, all end-of-treatment evaluations will be performed. For participants who withdraw for reasons other than disease progression, imaging assessments will remain mandatory.

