### Follow-up procedure

2.11

Participants allocated to the adjuvant TACE group will receive a single TACE procedure following hepatic angiography, followed by standardized intensive follow-up, whereas those in the intensive follow-up group will undergo surveillance alone after angiography. Follow-up assessments will be conducted every 3 months (±7 days) from the time of first intervention, and every 6 months (±7 days) after 2 years. At each visit, participants will undergo comprehensive evaluation, including contrast-enhanced CT or MRI of the chest and upper abdomen, measurement of tumor markers such as alpha-fetoprotein and abnormal prothrombin, and additional assessments as detailed in Table 1.

**Table 1 tbl1:** Schedule of study assessments and study timeline.

Phase	Screening period	TACE treatment period	Safety Visit o	Survival Visit p
		C1/D1		
Days	−28∼-1	1	30 days Post-TACE	Every 90 days
Time Window (Days)	NA	+3	±7	±7

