
o Safety follow-up will be conducted at (30 ± 7) days after TACE treatment or prior to the initiation of any new antitumor therapy, whichever occurs first. All adverse events (AEs) that occur prior to the safety follow-up visit must be documented and followed until resolution to Grade 0–1 return to baseline status, or until the investigator determines that further follow-up is not clinically warranted based on appropriate justification (e.g., no reasonable expectation of recovery or clear clinical improvement), whichever occurs first. Serious adverse events (SAEs) occurring within 90 days after study treatment administration or prior to the initiation of subsequent antitumor therapy (whichever occurs first) must be continuously monitored and documented in detail until resolution, stabilization, or return to baseline clinical status, in accordance with protocol-defined safety reporting procedures.

p Survival follow-up will be conducted every 90 days (±7 days) after completion of the safety follow-up visit. These follow-up assessments may be performed via in-person visits or telephone contact, as appropriate, to collect survival status and relevant clinical information.

The participant timeline is illustrated in Fig. 1.

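### Section 2.9.4 claims masking of investigators and participants that the protocol's own procedures do not deliver, so imaging-confirmed RFS is open to differential ascertainment

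*Protocol article*

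**What the plan says.** Section 2.9.4 calls the design multiply blinded. Only the interventional doctor knows the arm, while "investigators, participants and data analysts will remain blinded throughout the study until unblinding".

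Other parts of the protocol article describe the trial as follows.

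- **Procedure (2.8).** In the TACE arm a catheter is placed superselectively at the resection margin, "followed by embolization using an emulsion of 50 mg lobaplatin and 3–5 mL ethiodized poppyseed oil". In controls, "hepatic arteriography will be performed without administration of embolic or chemotherapeutic agents". Only local anesthesia is described: "After local anesthesia with 5 mL of 2% lidocaine at the right femoral artery puncture site".
- **Order of events (2.6, 2.8, 2.9.1).** Randomization follows an angiogram free of tumor staining. TACE may follow randomization by up to one week.
- **Visit clocks (2.11; Table 1, notes n and o).** Section 2.11 counts visits in both arms from the first intervention and asks for "contrast-enhanced CT or MRI of the chest and upper abdomen". Note n starts tumor imaging at the first dose of investigational treatment. Note o says: "Safety follow-up will be conducted at (30 ± 7) days after TACE treatment".
- **Investigator tasks (2.15.2, 2.17.2; note n).** Investigators complete the CRFs. Adverse events are recorded with their relationship to the intervention. Under note n the investigator judges whether investigational treatment goes on after progression is first seen on imaging.
- **Primary endpoint (2.1).** RFS runs from randomization to imaging-confirmed recurrence or death from any cause. The article does not say who reads the images.

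**The concern.** The masking statement is categorical, but the operating instructions are written as if staff know who had TACE and when. Both cannot be right.

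This matters because recurrence, unlike death, is a judgment made on scans of the treated region, and its date depends on when scans are taken. If those who schedule scans, record findings or judge them know the arm, recurrences can be called earlier, later, more often or less often in one arm. If the imaging clock starts from an event that only one arm has, the timing of looks can differ even without any conscious bias.

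The Introduction and Discussion also state the expectation that TACE adds nothing after a truly curative resection, so opinions about the arms are already formed. Left as it stands, Section 2.9.4 would let the final report present RFS as a blinded endpoint when the document does not secure that.

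**Working it through.** **Step 1. Test the masking claim group by group.**

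*Investigators.* A visit dated 30 days after TACE can be scheduled only by someone who knows whether and when TACE was given. For a control the date is undefined. The same holds for note n's imaging clock and for its provision that the investigator decides whether investigational treatment continues. That provision sits oddly in a single-session trial, but as written it presupposes knowledge of the arm. Recording the relationship of an adverse event to the intervention is weaker evidence taken alone, because a masked investigator can record a provisional attribution. Together with a TACE-dated safety visit and CRFs completed by the same people, the claim is not supported.

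*Participants.* Both arms have a femoral puncture and an angiogram, which gives partial masking. Against that, the described anesthesia is local only, one arm has the extra superselective catheterization and embolization, and no sham is described. In addition, if randomization follows the angiogram and TACE may come up to a week later, the literal reading allows a second catheterization in the TACE arm only. If TACE is always done in the same session, the one-week allowance has no purpose. Masking of participants is therefore doubtful rather than disproved.

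*Analysts.* Nothing in the document contradicts their masking.

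**Step 2. Set the clocks side by side.**

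| Source | Starts from | Defined for controls? |
|---|---|---|
| Section 2.11 | first intervention | only if the angiogram counts as one |
| Note n | first investigational treatment | no |
| Note o | TACE | no |

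The imaging intervals also differ: 3-monthly and then 6-monthly after 2 years in Section 2.11, against 6-weekly and then 12-weekly after 54 weeks in note n.

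**Step 3. Reproduce the plan's event number.** Section 2.12 uses a margin of 1.4, one-sided alpha 0.025, 80% power and 1:1 allocation.

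- Events = 4 × (1.960 + 0.842)² / (ln 1.4)² = 4 × 7.849 / 0.1132 = 277.3, so 278, or 139 per group as stated.
- With a 16.1-month median, 12 months' uniform accrual and 24 months' minimum follow-up, the event probability is 0.722. Then 277.3 / 0.722 = 384, also as stated.

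**Step 4. Illustrate what a shift would do.** The apparent HR r below is an assumption, not an estimate. With 278 events the standard error of ln HR is 2/√278 = 0.120, so 1/SE = 8.337. With a true HR of 1:

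false superiority = Φ(−ln r × 8.337 − z), with z = 1.645 (one-sided 0.05, Section 2.13) or 1.960 (one-sided 0.025, Section 2.12).

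| Apparent HR | One-sided 0.05 | One-sided 0.025 |
|---|---|---|
| 0.95 | Φ(0.428 − 1.645) = 11% | Φ(0.428 − 1.960) = 6% |
| 0.90 | Φ(0.878 − 1.645) = 22% | Φ(0.878 − 1.960) = 14% |

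If the true HR is at the 1.4 margin, the same proportional shifts give false noninferiority of 6% and 14%, against a nominal 2.5%.

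The bias could equally run against TACE. With an apparent HR of 1/0.95 = 1.053, false superiority falls to Φ(−0.428 − 1.645) = 2%. Power for noninferiority when the true HR is 1 falls from 80% to Φ((0.336 − 0.051) × 8.337 − 1.960) = Φ(0.418) = 66%.

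**The case against.** The strongest objection is that the article nowhere says site investigators read the endpoint images. A condensed article may leave masked central reading to the full protocol, and its silence is not a defect. That stands. A reader might infer that RFS is called by unmasked site investigators and is in effect open-label, but the document does not establish this. Masked reading would protect the endpoint. It would not make the statement about investigators in Section 2.9.4 true.

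Several supporting arguments are also weak and carry no weight here.

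- Section 2.7 says "Participants in the intensive follow-up group will avoid unnecessary treatment-related costs and potential adverse effects". This is a rationale for adherence and does not say that participants learn their arm.
- The staff member who opens the envelope (2.9.3) must inform the operator, and nothing says this person assesses outcomes.
- That the oil stays visible on later CT is general knowledge and is not stated in the article. MRI is also allowed.
- TACE-keyed wording in Table 1 may be carried over from a template, since the notes also mention Cycle 2 in a single-session trial. Table 1 does not say that controls skip the 30-day visit. The wording still governs conduct until it is corrected.

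Finally, any rate of late or missed recurrence calls would be unsourced. Deaths would be unaffected, and recurrences away from the treated margin would be less exposed to any local masking by oil. The expectation of no benefit could push judgment against TACE as easily as for it. This is why no bias is estimated here.

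**Conclusion.** Section 2.9.4 is wrong as written for investigators, doubtful for participants and unchallenged for analysts. Imaging-confirmed RFS is open to differential ascertainment. The document does not show that such bias will occur, in which direction, or how large it would be.

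The illustration gives scale only. It assumes 278 events, proportional hazards and a 5% artefactual shift in the HR. In favor of TACE, that shift roughly doubles the one-sided 5% error to 11%; against TACE, it cuts noninferiority power from 80% to 66%.

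The contradiction itself rests on the procedural sections alone. It needs neither an assumption about who reads the scans nor one about whether the oil is visible.

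**What to change.** 1. **Restate Section 2.9.4 to what the design delivers.** Analysts are masked, and participants are masked as far as possible. The operator, the person who opens the envelope, and staff who handle TACE-specific visits or adverse-event causality are not masked. Do not describe RFS as a blinded endpoint unless its readers are in fact kept masked, and if so, say how.
2. **Use one day 0 in both arms.** Count safety and imaging visits from the angiography, which both arms undergo. Reconcile Table 1 and notes n and o with Section 2.11 accordingly, including the differing imaging intervals. Reconcile the one-week allowance in Section 2.9.1 with randomization after angiography. Which intervals and timing to keep is for the sponsor to settle.
3. **Keep allocation off imaging requests.** This is a minor safeguard. It would not mask a reader who can see oil on the scan.
4. **Treat any analysis of recurrences away from the resection margin as supportive only.** It removes events where TACE is delivered. Section 2.6 also lists recurrence among the reasons for ending follow-up, so later distant recurrences may go unseen. Margin recurrence should be handled as a competing event.

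The cost of items 1 to 3 is protocol wording and one common reference date, with no new procedures. The small downside is that the trial can no longer be described as fully blinded.

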#### Unblinding procedures

2.9.5

Emergency unblinding may be conducted in the event of a medical emergency or upon request by regulatory authorities.

### Concomitant medications during the study

2.10

All medications administered within 30 days prior to screening and all concomitant medications used during the study period will be documented in the electronic case report form.

Supportive treatments permitted during the study include antiviral therapy for hepatitis B virus or hepatitis C virus infection,^35^ antibiotics, analgesics, hormonal therapies, intravenous fluid support, psychological interventions, palliative surgical procedures, and other measures necessary for symptom management.

Participants are prohibited from initiating any medications without prior investigator approval in the absence of disease recurrence or metastasis. From study entry until 120 days after the final study intervention, the use of investigational agents, antitumor therapies, immunosuppressive drugs, and live vaccines is strictly prohibited.

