#### Criteria for discontinuation

2.6.3

Participants may discontinue study treatment or be withdrawn prematurely under the following conditions: initiation of antitumor therapy other than adjuvant TACE or antiviral therapy for hepatitis B or C after curative hepatectomy, including but not limited to anti-angiogenic tyrosine kinase inhibitors or immune checkpoint inhibitors; disease progression requiring modification of treatment strategy; occurrence of SAEs or intolerance to the study intervention (all SAEs and adverse events will remain included in safety analyses); withdrawal of consent by the participant; investigator-determined discontinuation for medical reasons; inadequate compliance with study requirements; confirmed pregnancy, which will also be reported as an SAE; use of prohibited concomitant medications or substances that may affect safety or efficacy assessments; development of a condition that substantially alters clinical status or study endpoints; diagnosis of a second primary malignancy; or death.

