### Sample size calculation

2.12

Sample size estimation was performed using PASS 2021 (version 21.0.3) for a noninferiority randomized controlled trial. Based on historical data from our center, the median RFS for patients with high-risk recurrence factors managed with intensive follow-up alone was 16.1 months,^13^ corresponding to a hazard rate of 0.043 (ln(2)/16.1). Enrollment is planned over 1 year, followed by at least 2 years of follow-up. With a one-sided α of 0.025, 80% power, and a 1:1 allocation ratio, 192 participants per group (total *n* = 384) are required to demonstrate noninferiority at a hazard ratio margin of 1.4, with an estimated 139 events per group. Assuming an annual attrition rate of 5%, an additional 58 participants are required, yielding a total sample size of 442.

Sensitivity analysis was conducted using an alternative median RFS of 19.0 months derived from a cohort excluding DSA-positive patients,^34^ corresponding to a hazard rate of 0.0365 (ln(2)/19.0). Under similar assumptions, 360 and 361 participants would be required in the experimental and control groups, respectively (total *n* = 721), to achieve 80% power at the same noninferiority margin. Given the practical constraints of an investigator-initiated study without commercial funding, enrollment of more than 700 participants is not feasible; therefore, a target sample size of at least 442 participants has been selected to ensure study reliability.

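### The 120-day ban on antitumor therapy has no exception for recurrence and conflicts with other sections that foresee such therapy in the same window

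*Protocol article*

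**What the plan says.** Section 2.10 (Concomitant medications during the study) holds two restrictions, one after the other. The first bars participants from starting any medication "without prior investigator approval in the absence of disease recurrence or metastasis". The second starts at study entry and reads: "until 120 days after the final study intervention, the use of investigational agents, antitumor therapies, immunosuppressive drugs, and live vaccines is strictly prohibited". Only the first mentions recurrence, and only the second has an end date.

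Other sections bear on the same therapy:

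- Section 2.6 (Patients) names disease progression and the start of a new antitumor therapy among the landmarks that end follow-up, at any time.
- Section 2.6.3 (Criteria for discontinuation) lists "disease progression requiring modification of treatment strategy" and, separately, "initiation of antitumor therapy other than adjuvant TACE or antiviral therapy for hepatitis B or C after curative hepatectomy". Neither has a time limit.
- Table 1, note o, sets the safety visit at 30 ± 7 days after TACE "or prior to the initiation of any new antitumor therapy, whichever occurs first". It also follows SAEs for 90 days or until subsequent antitumor therapy.
- Section 2.8 (Interventions) states: "Adjuvant TACE will be administered as a single session only". The intensive follow-up arm has angiography without any embolic or chemotherapeutic agent.
- Section 2.9.1 (Sequence generation) states: "The interval between randomization and administration of adjuvant TACE will not exceed 1 week".

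**The concern.** A site that finds recurrence at an early scan has two answers in the same document. Section 2.10, taken as written, forbids antitumor therapy until day 120. Sections 2.6 and 2.6.3 and note o proceed as though such therapy can begin. The trial runs in more than ten hospitals, which may not all resolve this in the same way.

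The stake is first the care of participants with early recurrence. It is then overall survival, a key secondary endpoint, because the timing of treatment after recurrence could depend on how a site reads the text. RFS is not affected by this part of the problem, since the RFS event has already occurred when the conflict arises.

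Two smaller mismatches concern the time before recurrence. The ban stops at day 120, whereas Section 2.6.3 treats other antitumor therapy as a discontinuation reason without limit. And the wording in Section 2.6.3 that sets adjuvant TACE apart is tied to neither arm nor session, whereas Section 2.8 allows one session in one arm.

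**Working it through.** **Does the conflict fall inside the window?** TACE is a single session given at most 1 week after randomization, so the 120-day clock starts once, close to randomization. For the intensive follow-up arm I take angiography as the study intervention.

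| Event | Source | Approximate day | Within 120 days? |
|---|---|---|---|
| Scans at weeks 6 and 12 | Table 1, note n | 42 and 84 | Yes |
| First scan at 3 months | Section 2.11 | 90 | Yes |
| Safety visit, or earlier if new antitumor therapy starts | Table 1, note o | 30 ± 7 | Yes |
| SAE window, or earlier if subsequent antitumor therapy starts | Table 1, note o | up to 90 | Yes |
| Progression leading to a change of treatment | Section 2.6.3 | any | Can be |
| New antitumor therapy as a landmark | Section 2.6 | any | Can be |

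Recurrence can therefore be confirmed inside the window under either imaging schedule.

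**Check of the protocol's own model.** Section 2.12 states that "the median RFS for patients with high-risk recurrence factors managed with intensive follow-up alone was 16.1 months". The other inputs there are a margin of HR 1.4, one-sided α 0.025, 80% power, 12 months of accrual and 24 months of further follow-up.

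- Events: 4 × (1.960 + 0.842)² / (ln 1.4)² ≈ 278, or 139 per group, as stated.
- Hazard: λ = ln 2 / 16.1 = 0.04305 per month.
- Event probability with uniform accrual: 1 − (e^(−24λ) − e^(−36λ)) / (12λ) = 0.722.
- Sample size: 278 / 0.722 = 385, against 384 stated.
- Attrition: 384 × 1.15 = 441.6, which rounds up to the stated 442.

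The constant-hazard model reproduces the plan, so I use it for the share of early events.

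**RFS events by day 120.** 120 days / 30.4375 = 3.94 months.

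- Median 16.1 months: 1 − exp(−0.04305 × 3.94) = 15.6%; × 442 = 69.
- Median 19.0 months (the sensitivity value in Section 2.12): λ = 0.03648; 1 − exp(−0.03648 × 3.94) = 13.4%; × 442 = 59.

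RFS runs from randomization and the ban from the intervention. If the full permitted week separates them, the window ends at day 127 (4.17 months) and the figures become 16.4% (73) and 14.1% (62), which changes little.

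**What these counts include.** They contain deaths, and they contain recurrences that no scan has yet shown. By day 90 (2.96 months), the first scan in Section 2.11, the same formula gives 12.0% (53) and 10.2% (45), again with deaths. A recurrence found at that scan has about 30 days of the ban left. The 6-weekly schedule in note n would find some earlier.

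**The case against.** The best defence is that the sections should be read together. The sentence just before the ban limits its restriction to participants without recurrence, and the authors may have meant that to govern the whole paragraph. Section 2.6.3 foresees a change of treatment at progression, Table 1 collects subsequent antitumor treatment, and no passage tells a site to withhold treatment from a participant whose disease has recurred. This makes the intended meaning plausible but does not remove the conflict. The qualifier is absent from the ban itself, and the ban is worded as strict.

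Note o can also be defended as contingency wording: a protocol may forbid a therapy and still say when a visit takes place if it is given. That weakens note o as evidence on its own. It does less for Section 2.6.3. The study treatment is one session, so a change of treatment strategy at progression can hardly mean anything except a new treatment.

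A reader might go further and infer that restrictions lapse at day 120, leaving most of the RFS period open to other adjuvant therapy and pulling the arms together. The model does put about 78% to 80% of expected RFS events after day 120. But the investigator-approval sentence in Section 2.10 and the discontinuation reason in Section 2.6.3 have no end date, so control continues in another form. The word may in Section 2.6.3 does not show tolerance either, since it governs the whole list, including withdrawal of consent and death.

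A reader might likewise infer that TACE is open to the intensive follow-up arm. Sections 2.6, 2.8 and 2.11 give that arm surveillance only, and TACE there would fall under inadequate compliance in Section 2.6.3. What remains is loose wording.

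**Conclusion.** The point holds as an internal contradiction. The ban in Section 2.10 carries no exception for recurrence, other sections foresee antitumor therapy in the same period, and scheduled scans make the situation likely to arise. At most about 13% to 16% of participants (59 to 69 of 442) would have an RFS event by day 120. That assumes a constant hazard, the control medians in both arms and a clock starting at randomization; the number who actually face the conflict is lower. The mismatches between Section 2.6.3 and Sections 2.10 and 2.8 are secondary.

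No bias in the RFS comparison is established. The documents give no rate of off-protocol antitumor therapy in participants without recurrence, so neither the presence nor the size of any dilution can be derived from them.

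**What to change.** Reconcile Sections 2.6, 2.6.3, 2.8 and 2.10 and Table 1, note o, so that one consistent statement says how the restriction on antitumor therapy applies before and after imaging-confirmed recurrence. In the same pass, make the time limit in Section 2.10 agree with the open-ended reason in Section 2.6.3, and make the reference to adjuvant TACE in Section 2.6.3 agree with Section 2.8. What the rule should be is for the sponsor to decide.

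Report by arm, with start dates, any antitumor therapy begun before recurrence. Concomitant medications (Section 2.10) and subsequent antitumor treatment (Table 1) are already collected, so this needs no new data. The cost is amendment wording, its submission to the ethics committees under Section 2.17.4, and one descriptive table. The sample size and the primary analysis are unchanged.
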